#### Qualitative analysis

In line with our previous work involving qualitative evaluation of SBNT [46], interviews will be recorded and transcribed verbatim for analysis. Thematic analysis will be used to analyze the data, and the findings will be presented to a selection of the original participants to check the validity of the resulting interpretation [47].

#### Economic analysis

The economic analyses will focus on logistical issues such as the acceptability, feasibility and reliability of the data collection instruments in this trial population. Information will be collected on length of time taken to complete each instrument, analysis of missing responses and exploration of psychometric properties. Descriptive statistics will be computed for the EQ-5D and the ICECAP-A, and the within-individual difference in mean quality-of-life scores will be tested. The evaluation will be conducted from both a healthcare and a societal perspective. The analyses will be a within-trial cost-effectiveness analysis based on the primary outcome of ‘abstinence from heroin’ (for example, the difference in primary outcome between the intervention arm and the other two arms of the trial). A secondary analysis will be a cost-utility analysis using quality-adjusted life years as the outcome. A decision-tree model [48] will be used that will adopt an incremental approach and focus on the differences in cost and outcomes between the trial arms. Appropriate one-way and multi-way deterministic sensitivity analysis will be carried out to test the robustness of the results [49]. The choice of variables to assess as part of the sensitivity analysis will be confirmed when the data collection is complete but will focus on the modeling variables which are the most uncertain and for which there is the greatest amount of sampling variability.

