#### Economic evaluation

The economic evaluation will be conducted from a societal perspective, incorporating the widest measurement of costs and outcomes as possible. The base-case analysis will estimate the incremental cost-effectiveness of B-SBNT versus the two other treatment conditions using the primary outcome of abstinence of heroin. Further analyses will incorporate additional outcomes measured from the perspective of the patients and network members and will include assessment of ‘capability wellbeing’ as measured by the Investigating Choice Experiments Capability measure for Adults (ICECAP-A) [42] and health status as measured by the EQ-5D [43] at baseline, 3 months and 12 months. Health service and criminal justice service resource use will be measured using the Client Service Receipt Inventory [44], and will include number of general practitioner visits, outpatient and inpatient visits, community care and drug-related services, criminal justice service costs and medication use. Unit costs will be obtained from standard sources.

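### The only uncertainty method named for the economic results is deterministic sensitivity analysis, yet it is aimed at sampling variability, which it cannot propagate

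*Protocol article*

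**What the plan says.** All of this is in the protocol article.

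- **Estimand.** Economic evaluation: "The base-case analysis will estimate the incremental cost-effectiveness of B-SBNT versus the two other treatment conditions using the primary outcome of abstinence of heroin".
- **Type of analysis.** Economic analysis: "The analyses will be a within-trial cost-effectiveness analysis based on the primary outcome", with a secondary cost-utility analysis on quality-adjusted life years.
- **Vehicle.** "A decision-tree model [48] will be used that will adopt an incremental approach and focus on the differences in cost and outcomes between the trial" (the quote is cut there; it refers to the randomized groups).
- **Robustness.** "Appropriate one-way and multi-way deterministic sensitivity analysis will be carried out to test the robustness of the results". The inputs to vary are to be settled once data collection is over, but the analysis will "focus on the modeling variables which are the most uncertain and for which there is the greatest amount of sampling variability".
- **Emphasis.** The same section opens: "The economic analyses will focus on logistical issues such as the acceptability, feasibility and reliability of the data collection instruments in this trial population".

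Neither economic section mentions a bootstrap, a probabilistic sensitivity analysis, an acceptability curve, or an interval for incremental cost, incremental effect or net benefit. The one test mentioned concerns within-individual change in quality-of-life scores, which is not an incremental economic quantity.

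**The concern.** Deterministic sensitivity analysis answers a what-if question: how the result moves if an input takes another value. That suits unit costs, perspective and the structure of the tree. Sampling variability poses a different question: how far the estimated incremental cost and effect could lie from the truth because only 40 people were observed per arm. Answering it needs the joint sampling distribution of the two, including the correlation between a participant's costs and outcome. The article identifies sampling variability as a main source of uncertainty and then assigns it a tool that cannot propagate it.

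At stake is how firm the ratio looks. A point estimate with a table of scenarios can appear stable when the data are compatible with no gain in abstinence, or with a cost difference of either sign. The inputs to vary are also chosen after the data are in, so apparent robustness depends partly on that choice.

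**Working it through.** **Inputs from the article.** 120 participants, 40 per arm (Sample size). Abstinence of 0.3 and 0.1 are given there as possible B-SBNT proportions.

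**Inputs assumed.** Comparator abstinence of 0.2 or 0.1. Cost coefficient of variation (CV), and for the illustration mean costs of 1300 v 1000 units; the article gives no cost figures. Complete data on all 40 per arm, which is the best case.

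**1. The article's own precision figures.** There is no economic figure to reproduce; the only precision statement is for a single arm's proportion. With p ± 1.96·√(p(1−p)/40), p = 0.1 gives 0.007 to 0.193, matching the stated 0.01 to 0.19. For p = 0.3 the result is 0.158 to 0.442. The stated upper limit of 0.44 agrees and the stated lower limit of 0.18 does not. That mismatch is a separate matter and nothing below depends on it.

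**2. Incremental effect.** d ± 1.96·√(p₁(1−p₁)/40 + p₂(1−p₂)/40):

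| B-SBNT v comparator | d | SE | 95% CI |
|---|---|---|---|
| 0.3 v 0.2 | 0.10 | √(0.00525+0.00400) = 0.096 | -0.09 to 0.29 |
| 0.2 v 0.1 | 0.10 | √(0.00400+0.00225) = 0.079 | -0.05 to 0.25 |
| 0.3 v 0.1 | 0.20 | √(0.00525+0.00225) = 0.087 | 0.03 to 0.37 |

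Whether the interval includes zero depends on the assumed comparator.

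**3. Incremental cost.** With equal means and CVs in the two arms, the half-width as a share of mean cost is 1.96·CV·√(2/40) = 0.438·CV. That is 44%, 66% and 88% for CV 1, 1.5 and 2.

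**4. What a deterministic range would show.** Suppose, generously, that each input is moved to its 95% limits. With a cost difference of 300 and 0.3 v 0.2, the ratio is 300/0.10 = 3000. At the upper effect limit it is 300/0.2885 ≈ 1040. At the lower limit it is 300/(−0.0885) ≈ −3390, having passed through an undefined value at zero. With 0.3 v 0.1 the ratio is 300/0.20 = 1500, and the two limits give about 810 and 9900. Moving both inputs at once describes a box that covers 0.95² ≈ 0.90 if cost and effect differences are independent; with correlation the coverage is something else, which the method does not estimate. Neither exercise yields an interval with known coverage for the ratio or for net benefit.

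**5. What a joint analysis would show.** 20,000 simulated trials, 40 per arm, gamma costs with means 1300 v 1000, binomial abstinence, cost and outcome drawn independently:

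| CV | 95% range of cost difference (0.3 v 0.2 runs) | More costly and more effective, 0.3 v 0.2 | Same, 0.3 v 0.1 |
|---|---|---|---|
| 0.5 | 46 to 559 | 81% | 98% |
| 1.0 | -204 to 822 | 71% | 87% |
| 1.5 | -442 to 1090 | 64% | 77% |

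The effect difference was zero or negative in about 18% of the 0.3 v 0.2 trials (for example 0.163 + 0.022 at CV 1) and about 1.5% of the 0.3 v 0.1 trials. A deterministic table does not supply such joint proportions.

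**The case against.** The strongest reply is that the article is a condensed account. It says deterministic analysis will be done; it does not say nothing else will. Major analyses are deferred to a statistical analysis plan that is not shown, and bootstrapping or acceptability curves are details an article often leaves to such a plan. This stands against a stronger reading that a reader might draw: that uncertainty will be examined by deterministic analysis alone and the economic result will therefore carry no valid interval. The text does not support that, because it excludes neither a bootstrap nor an interval. It does not dispose of the narrower point, which rests on a stated method and a stated target that do not fit together.

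Second, the economic work is described as focusing on feasibility. The Discussion makes progression to a definitive trial depend on an indication of positive change in the main outcome, its standard deviation and recruitment, not on cost-effectiveness. This stands and limits the consequence. It does not remove it: the article still commits to incremental results across three arms, and the Discussion describes the economic evaluation as comprehensive.

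Third, one-way and multi-way analysis is a coherent companion to a decision tree, and the ranges could be set at confidence limits from the trial. That is fair, since the article does not say how ranges will be set. Step 4 shows why even that choice gives no joint coverage.

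Fourth, the sizes depend on inputs not in the article. This is correct, so the assumptions are labelled and more than one contrast is shown, including one that excludes zero.

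**Conclusion.** The concern holds in limited form. The only uncertainty method named for the cost-effectiveness and cost-utility results is deterministic, and the article directs it at sampling variability, which it cannot propagate. With 40 per arm that uncertainty is material. The half-width for the incremental effect is about 0.16 to 0.19 over the contrasts examined, so a true difference of 0.10 would not be distinguished from zero, while one of 0.20 (0.3 v 0.1) would be, narrowly. For costs the half-width is about 44% to 88% of mean cost if the CV is 1 to 2.

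These sizes rest on assumed comparator abstinence, assumed cost distributions and complete data; the simulation also assumes independence of costs and outcomes. The mismatch between method and target does not depend on any of them. It would also be too strong to say that the ratio is bound to be uninformative, since that turns on results not yet known. This is a worthwhile correction to a feasibility-oriented secondary component, with no bearing on the trial's stated progression criteria.

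**What to change.** Amend Economic analysis so that sampling uncertainty has its own method, or cross-refer to a plan that already provides it:

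- Use a non-parametric bootstrap that resamples participants within arm and keeps each person's costs and outcome together, re-estimating the tree's inputs in each resample. Alternatively, run a probabilistic analysis of the decision tree with distributions derived from the trial data, including the correlation between costs and outcomes.
- Report intervals for incremental cost, incremental effect and net benefit, with the cost-effectiveness plane and acceptability curves for B-SBNT, PGS and TAU.
- Keep one-way and multi-way deterministic analysis for unit-cost and structural assumptions, and drop sampling variability as its target.

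The cost is some rewording and a little extra programming on data already being collected. No additional participants or measurements are needed.

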### Ethics

This study has received approval from the National Research Ethics Committee: The Black Country (REC number: 12/WM/0046; approved 08/05/2012).

## Discussion

The National Institute for Health and Clinical Excellence has highlighted the evidence for psychosocial treatments for heroin dependence [50], and family/social network interventions are promising for two reasons: (1) by involving family and friends in the treatment process there are opportunities for generalization of the effects beyond an episode of professional treatment; and (2) treatment may reduce the considerable physical and psychological health burden of drug misuse on family and friends.

The B-SBNT intervention has been specifically adapted to make it more suitable for use within UK drug treatment services by using the elements found to be most important in the process of drug-use change [24]. This study aims to establish the feasibility of delivering a social network-based treatment for patients receiving OST within NHS drug services, as well as the impact of the intervention on both short (3 months) and longer-term outcome (12 months) for patients and their family members. Evaluation of the efficacy of B-SBNT will involve quantitative and qualitative methodology, and the trial will involve a comprehensive economic evaluation.

This study will recruit and follow-up family members of patients in UK NHS drug treatment within a randomized controlled trial design, and the results will inform the feasibility of recruitment of family members in a larger confirmatory trial with the potential to help further our understanding of the impact of drug use on family members, as well as the benefits to family members from inclusion in the drug treatment process.

The study will quantify various elements of uncertainty around the delivery of social network interventions in the OST population, and the measurement of its effectiveness: the feasibility of recruiting and training staff (that is, number willing to be trained, levels of attendance at training and supervision sessions, degree of adherence to the treatment manuals, level of staff satisfaction with the training and the interventions); the feasibility of recruiting patients (that is, number wishing to participate, attendance at assessment sessions, attendance at intervention appointments, client satisfaction with B-SBNT); the feasibility of recruiting network members into the treatment process (that is, numbers agreeing to participate, attendance at appointments, level of acceptance of B-SBNT treatment); the feasibility of recruiting family members to evaluate the impact of the intervention on their health (that is, number of family members recruited and interviewed, acceptance of the measures of symptoms and coping); and the feasibility of employing the chosen research procedures in clinical services (that is, recruitment methods, including giving information and obtaining consent), randomization, intervention delivery and outcome measurement).

In order for this study to lead to a definitive trial it will need to provide an indication of positive change in the main outcome measure for the social network intervention. However, it will also be important to know the standard deviation of this measure to determine if the required sample size for a definitive trial is realistic. The study will tell us whether participating centers are likely to recruit a sufficient number of participants to deliver a full trial within a reasonable timescale.

Research demonstrates significantly better outcomes for drug-using individuals, such as reduced risk of drug relapse and better response to treatment, when there is positive social support for change [10-14]. However, at present no available model exists to implement a family and social intervention in routine practice in the UK NHS drug treatment system. Furthermore, there is very limited knowledge of the composition and potential availability of supportive social networks to people in drug treatment services. This study is an important step in the development of evidence and aims to address these gaps in the literature. It is hoped that the results of the study will help to inform future service provision in drug treatment services for patients receiving OST.

## Trial status

The trial is currently in the recruitment phase.

## Abbreviations

B-SBNT: Brief Social Behavior and Network Therapy; EQ-5D: European Quality of Life; : ICECAP-A,; MAP: Maudsley Addiction Profile; NHS: National Health Service; NTA: National Treatment Agency; OST: opiate substitution therapy; PGS: Personal Goal Setting; SBNT: Social Behavior and Network Therapy; TAU: treatment as usual; UKATT: UK Alcohol Treatment Trial.
